### Study population

#### Criteria

The inclusion criteria for PwMS are a confirmed MS diagnosis, and for HCs the absence of an MS diagnosis. For all, the inclusion criteria are an age between 18 and 70 years, the ability to participate in a short NPA, as judged by the practitioner and/or researcher, and an adequate command of the Dutch language. The exclusion criterion for both PwMS and HCs is the presence of other neurological and/or major psychiatric conditions.

#### Recruitment

PwMS are recruited from the Neurology Unit of the University Medical Centre Groningen (UMCG), Martini Hospital Groningen (MHG) and Medical Centre Leeuwarden (MCL), the Netherlands. PwMS who have been scheduled for regular clinical visits at the outpatient department will be approached by their practitioner and provided with information regarding the study and an informed consent form. In addition, PwMS can independently sign up for participation whenever they hear about the study, e.g., through patient associations. PwMS who sign up for the study themselves will be contacted by the researchers, after which the study information and informed consent form will be sent to their home address. A group of 100 HCs, matched for age and education level, will be recruited through convenience sampling.

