**General information (participants)**					
Demographics	Age, sex, education	✓	✓		✓
Medical information	EDSS^c^, disease duration, MS^d^ subtype, MS medication	✓			✓
Anamnesis (structured interview)	Sleep, coping, social network, subjective complaints, highest burden	✓	In part	✓	✓

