### Data collection

#### Primary outcome

The primary outcome of the MS-CEBA study are the CEBA profiles, which are latent and thus need to be derived from the scores on neuropsychological tests and questionnaires used to assess the CEBA domains. Through the use of a latent profile analysis, as described in the *Statistical Analysis* section, CEBA profiles will be revealed based on the raw scores of the tests and questionnaires used.

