### Statistical analysis

For analysing the data, Statistical Package for the Social Sciences (SPSS) version 28.0 and/or R, possibly combined with Latent GOLD version 6.0 [50], depending on the availability of suitable packages in R, will be used. For all analyses, the nominal significance level will be set at α = 0.05, 2 sided. The numbering of the analyses described below corresponds to the numbering of the objectives displayed in Table 1*.* In the following, T0 refers to the first group of 300 PwMS, and T1 refers to the retesting of 54 PwMS.

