**Phase 1: Identification of possible CEBA profiles.** 1a) Summary statistics will be computed, describing percentages of PwMS (n = 300) with CEBA symptoms, based on scores on the neuropsychological tests and questionnaires regarding each CEBA domain; 1b) MANOVAs with follow-up ANOVAs will be computed comparing PwMS *(n* = 300) to HCs (*n* = 100) on scores on the neuropsychological tests and questionnaires regarding the Cognitive and Behavioural domain, and ANOVAs will be computed comparing PwMS to HCs on scores on questionnaires regarding the Energetic and Affective domain; for 1c) and 1e) a three-step mixture analysis will be computed [51]: step 1 is a latent profile analysis to identify clusters of PwMS with common CEBA profiles; step 2 is to estimate the posterior cluster membership probabilities of the model from step 1 for each PwMS in the sample, and step 3 is to relate the cluster membership probabilities from step 2 to relevant predictors, i.e., a regression analysis will be carried out to estimate the relationship between the CEBA profiles and the demographic and disease-related variables, with an adaptation to account for the fact that cluster membership is estimated, rather than observed; for 1d) repeated measures MANOVAs will be computed comparing T1 (n = 54) to T0 (n = 300) on the scores on neuropsychological tests and questionnaires for the Cognitive and Behavioural domain separately; if a time effect is indicated, these will be followed by post hoc analyses (repeated measures ANOVAs), to assess which variable(s) the time effect pertains to. A repeated measures ANOVA will be computed comparing T1 to T0 on the scores on questionnaires regarding the Energetic and Affective domain separately; 1f) regression analysis will be carried out, considering two competing models: model 1, using the membership of the CEBA profiles as a predictor; and model 2, using the most distinguishing outcome variables (scores on neuropsychological tests and questionnaires in each of the CEBA domains) as predictors.

**Phase 2: Validation of CEBA profiles and development of the CEBA screening instrument.** 2a) The posterior cluster membership probabilities of the selected latent profile model from Phase 1 will be estimated for each of the PwMS in the new sample (n = 100). The equality of the distributions of membership probabilities of the new sample and Phase 1 sample will be tested using a chi-square test. 

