### Sample size

The sample size calculations provided below were performed following *G*Power* [52]. Since for objective 2b and objectives 3a and 3b (Table 1), no statistical analyses will be carried out, a sample size calculation is not relevant for these objectives.

With regard to objectives 1a and 1c, here, the main study parameter is the CEBA profile, which is latent and thus needs to be derived from performance on neuropsychological tests and questionnaires regarding the CEBA domains. For identification of the CEBA profiles, latent profile analysis will be performed. A minimum sample size of 300 is suggested for latent profile analysis to ensure that there is sufficient power to estimate all model parameters and recover the true number of classes [53, 54]. Therefore, the aim is to include a minimum of 300 patients. For objective 1b, the main study parameters are possible differences between PwMS and HCs on neuropsychological tests and questionnaires regarding symptoms in the different CEBA domains, which will be investigated through the performance of MANOVAs and ANOVAs. A power calculation (with a medium effect size [Cohen’s f] = 0.5, α = 0.05, power = 0.95) results in a minimal sample size of n = 60, which is expected to be exceeded with our goal of including 300 PwMS and 100 HCs for comparison of performance in the CEBA domains. With regard to objective 1d, here, the main study parameters are possible differences in CEBA symptoms between T0 and T1, which are derived from scores on neuropsychological tests and questionnaires regarding the CEBA domains. To investigate the extent to which individual CEBA symptoms are stable over time, repeated measures MANOVAs and ANOVAs will be performed to compare T0 to T1. Within-between interactions will be used. Here, a power calculation using repeated measure analysis (with medium effect size Cohen’s f = 0.5, α = 0.05, and power = 0.95) results in a total sample size of n = 54. Therefore, the aim is to include a minimum of 54 patients for comparing T0 to T1. Since objectives 1e and 1f, as well as objective 2a, depend on the CEBA profiles yet to be identified, the corresponding analyses are considered exploratory, and therefore, no sample size calculation will be provided at this stage. At a later stage, after the CEBA profiles have been identified, sample size calculations for these objectives will be provided, again using *G*Power* [52].

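### Objective 1b: sex is neither a matching variable for the healthy controls nor a term in the stated model, so any sex imbalance with the patients would go uncorrected

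*Protocol article*

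**What the plan says.** **Control selection** (protocol article, Recruitment): "A group of 100 HCs, matched for age and education level, will be recruited through convenience sampling". No other matching variable is named.

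**Model for 1b** (Statistical analysis, Phase 1): for the Cognitive and Behavioural domains, "MANOVAs with follow-up ANOVAs will be computed comparing PwMS" with controls. For the other two domains, "ANOVAs will be computed comparing PwMS to HCs on scores on questionnaires regarding the Energetic and Affective domain". Neither statement names a covariate.

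**Available data** (Table 2, general information): the row "Age, sex, education" is ticked for the Phase 1 patients and for the controls.

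**Demographics elsewhere**: the same section does use them for objective 1e, where a regression estimates the "relationship between the CEBA profiles and the demographic and disease-related variables". That analysis is within patients only.

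**Error level**: "For all analyses, the nominal significance level will be set at α = 0.05, 2 sided".

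**The concern.** Objective 1b asks whether patients and controls differ on the tests and questionnaires and, if so, in which domains. The comparison is not randomised. Patients come from three neurology units or sign themselves up, and controls are a convenience sample. Matching addresses age and education. Nothing in the sampling addresses sex, and nothing in the stated model does either.

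If the two groups differ in sex mix, and a score differs between men and women, part of the observed group difference reflects sex. A larger sample does not remove it. The exposure recurs for each such score across the follow-up ANOVAs.

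A smaller matter is that leaving age, sex and education out of the model forgoes whatever score variance they explain.

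**Working it through.** **1. The plan's own figure for 1b.** The Sample size section states "medium effect size [Cohen’s f] = 0.5, α = 0.05, power = 0.95" and gives a minimum of 60. A two-group one-way ANOVA with those inputs (noncentrality N × 0.5²) needs N = 54, so 60 is not reproduced under that reading. This is a separate matter: the planned 300 + 100 exceeds both figures, and nothing below depends on it.

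**2. Inputs for the bias.**
- From the document: 300 patients, 100 controls, two-sided α = 0.05.
- Assumed, because the document gives neither: a sex effect δ of 0.2, 0.3 or 0.5 SD on a score, and a difference Δp in the proportion female of 0.10, 0.20 or 0.30.

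**3. Formulas**, in units of the within-group SD:
- Spurious difference b = δ × Δp.
- SE = √(1/300 + 1/100) = 0.115.
- Type I error = Φ(−1.96 − b/SE) + 1 − Φ(1.96 − b/SE).

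**4. Results** (spurious difference in SD; type I error per test):

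| δ | Δp = 0.10 | Δp = 0.20 | Δp = 0.30 |
|---|---|---|---|
| 0.2 | 0.02; 0.053 | 0.04; 0.064 | 0.06; 0.081 |
| 0.3 | 0.03; 0.058 | 0.06; 0.081 | 0.09; 0.122 |
| 0.5 | 0.05; 0.072 | 0.10; 0.139 | 0.15; 0.255 |

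Worked middle cell: b = 0.3 × 0.20 = 0.06 and b/SE = 0.06/0.115 = 0.52, giving a type I error of 0.081. If δ = 0 or Δp = 0, then b = 0 and the error is 0.05.

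**5. Precision.** If the covariates explain a share R² of score variance (assumed; not in the document), the residual SD is multiplied by √(1 − R²). The difference detectable with 80% power is (1.960 + 0.842) × 0.115 × √(1 − R²).

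| R² | Detectable difference, 80% power (SD) | Power at 0.3 SD |
|---|---|---|
| 0 | 0.32 | 0.74 |
| 0.10 | 0.31 | 0.78 |
| 0.20 | 0.29 | 0.83 |
| 0.30 | 0.27 | 0.87 |

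The part due to sex alone is δ² × 0.21/(1 + δ² × 0.21), where 0.21 = 0.7 × 0.3 assumes 70% female. This gives about 1%, 2% and 5% for δ of 0.2, 0.3 and 0.5. Most of any gain would therefore have to come from age and education.

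**6. Is planned power at risk?** No. Without adjustment, 300 against 100 gives power 0.991 at 0.5 SD and above 0.99 at 1.0 SD, which is what f = 0.5 means for two equal groups.

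**7. Cost of adjusting.** At f = 0.5, with one to three covariates that explain nothing, the required N is 55 instead of 54.

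**The case against.** The strongest reply is that this is a condensed article, that covariate lists are commonly left to an analysis plan, and that a fuller plan may name them. This has weight, but it does not remove the point. The article states the matching variables and the model family for 1b, and in the same section it brings in demographics where it wants them (1e). The matching rule is also a recruitment decision, which a later analysis plan cannot undo.

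Other parts of the reply stand, and they limit the point:

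- **A reader might infer that the comparison is biased.** The documents do not show this. They give no sex mix for either group and no sex effect on any score. At the mild end of the assumed range, the type I error is close to nominal.
- **A reader might infer that 1b compares raw scores.** Raw scores are specified only for the latent profile analysis ("CEBA profiles will be revealed based on the raw scores of the tests and questionnaires used"). For 1b the text says only scores, so the accurate description is that no covariate is named.
- **A reader might infer residual imbalance in age or education.** The article does not say whether matching is individual or by group, so the bias argument rests on sex alone.
- **A reader might infer that 1b is underpowered, or that the profiles are affected.** Neither follows. The precision gain matters only for differences near 0.3 SD, which the plan does not target. The profiles are derived within patients, and controls do not enter that analysis or the Phase 2 replication.

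**Conclusion.** The point holds in conditional form. As written, sex is controlled neither by the selection of controls nor by the 1b model, although it is recorded in both groups. Any imbalance could therefore bias the comparison on scores that differ by sex.

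Under the assumed range, the spurious difference is 0.02 to 0.15 SD, with 0.06 SD in the middle case. The type I error per test is 5.3% to 25.5%, with 8.1% in the middle case. Even the largest of these is well below the 1.0 SD difference implied by the planning effect size, so the concern is with small to moderate differences wrongly declared or misjudged in size. The omission can be read directly from the text; the size of any bias cannot.

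Precision is a secondary benefit. This is an inexpensive improvement to a supporting Phase 1 objective and does not question the primary outcome.

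**What to change.** In the Statistical analysis section, specify 1b as MANCOVA with follow-up ANCOVAs, and ANCOVAs for the Energetic and Affective questionnaires (or equivalent linear models), with group, age, sex and education as terms. Report adjusted group differences with 95% CIs. In the Recruitment section, add sex to the matching variables for controls still to be recruited. The article reports 167 participants so far, without saying how many are controls, and recruitment planned to the end of 2026, so this may still be possible. If control recruitment is complete, the model change alone would deal with sex, to the extent that the model describes its effect adequately.

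The cost is about one sentence in each section. No new data are needed, and the effect on the required sample size is negligible.

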### Study procedures

#### Phase 1: Identification of possible CEBA profiles

Data collection and management of the 300 PwMS will be performed by the researchers (neuropsychologists). When informed consent is received, PwMS will be approached by the researcher to schedule the NPA. Prior to the NPA, PwMS will receive questionnaires regarding fatigue, mood, behaviour and societal participation to fill out at home (Table 2). The questionnaires will be sent digitally via the secure web app Research Electronic Data Capture (REDCap) [48, 49] or, upon request, on paper.

**Table 2 Tab2:** Overview of the assessments used in the MS-CEBA study

Assessment	Construct	Phase 1 PwMS^a^ *(n* = 300)	Phase 1 HCs^b^ (*n* = 100)	Phase 1 Retest PwMS (n = 54)	Phase 2 PwMS (*n* = 100)
**General information (participants)**					
Demographics	Age, sex, education	✓	✓		✓
Medical information	EDSS^c^, disease duration, MS^d^ subtype, MS medication	✓			✓
Anamnesis (structured interview)	Sleep, coping, social network, subjective complaints, highest burden	✓	In part	✓	✓
**Questionnaires (participants)**					
Hospital Anxiety and Depression Scale (HADS)	Anxiety and depression (Affect)	✓		✓	✓
Dutch Multifactor Fatigue Scale (DMFS)	Fatigue (Energy)	✓		✓	✓
Dysexecutive questionnaire (DEX)—self	Dysexecutive syndrome and behavioural changes (Behaviour)	✓		✓	✓
Impact on Participation and Autonomy questionnaire (IPA)	Participation	✓		✓	✓
**Questionnaires (proxies)**					
Dysexecutive questionnaire (DEX)—proxy	Dysexecutive syndrome and behavioural changes (Behaviour)	✓		✓	✓
Behavioural changes questionnaire	Behavioural changes (Behaviour)	✓		✓	✓
**Neuropsychological assessment (participants)**					
Symbol Digit Modalities Test (SDMT)	Information processing speed (Cognition)	✓	✓	✓	✓
15 Words Test (15-WT)	Verbal memory (Cognition)	✓	✓	✓	✓
Digit Span Test of the Wechsler Adult Intelligence Scale (WAIS) IV	Memory span/working memory (Cognition)	✓	✓	✓	✓
Trail Making Test (TMT)	Attentive/executive functioning (Cognition)	✓	✓	✓	✓
Letterfluency Test (LFT)	Attentive/executive functioning (Cognition)	✓	✓	✓	✓
Facial Expressions of Emotion: Stimuli and Tests (FEEST)	Social cognition (Behaviour)	✓	✓	✓	✓
^a^PwMS: People with Multiple Sclerosis; ^b^HCs: Healthy Controls; ^c^EDSS: Expanded Disability Status Scale; ^d^MS: Multiple Sclerosis					

Upon registration for participation, PwMS are asked to provide contact information about a proxy (e.g., significant other or other close relative). Informed consent for the proxy will also be obtained before study participation. The proxy is asked to fill out two questionnaires prior to the NPA appointment, either digitally via REDCap [48, 49] or on paper (Table 2). The proxy does not have to attend the NPA appointment.

The NPA takes approximately 90 minutes and consists of an anamnesis regarding demographic and disease characteristics, sleep, coping style, subjective complaints and highest experienced burden, and a neuropsychological test battery concerning different cognitive domains, including social cognition (Table 2). For the retest of Phase 1, PwMS who at administration for participation gave consent to be approached for possible follow-up research, will be asked to participate in the retest sample, after approximately one year.

From the group of 100 HCs, informed consent will be obtained before study participation as well. The questionnaires and test battery of the NPA will be the same as for the PwMS, but parts of the anamnesis (concerning disease characteristics, subjective complaints, and highest experienced burden), as well as proxy measures, will be excluded.

#### Phase 2: Validation of CEBA profiles and development of the CEBA screening instrument

For Phase 2, a new sample of 100 PwMS will be included following the same procedure for inclusion and assessment as in Phase 1 after approximately two years. Additionally, the development of the CEBA screening instrument will take place. In the event that symptoms in different CEBA domains prevail simultaneously within one CEBA profile, the highest experienced burden of the PwMS in question will be used to help select on which CEBA domain initial neuropsychological rehabilitation treatment should focus. The screening instrument will therefore consist of a concise set of neuropsychological tests and questionnaires identifying combinations of symptoms in the different CEBA domains combined with a short anamnesis regarding the highest experienced burden. Attached will be a manual outlining how to easily derive CEBA profiles from scores on the tests and questionnaires used, along with an advice regarding which neuropsychological rehabilitation treatment would be the most suitable for which combination of CEBA profile and highest experienced burden.

#### Phase 3: Evaluation of the recommended neuropsychological rehabilitation treatment

For the qualitative evaluation of Phase 3, PwMS from Phase 2 who sought neuropsychological treatment using the advice obtained with the screening instrument and who, at administration for participation, gave consent to be approached for possible follow-up research will be asked to share their experience with the recommended treatment in a qualitative evaluation. As a part of this, it will be evaluated whether the proposed method of treatment selection indeed proves appropriate.

### Data collection

#### Primary outcome

The primary outcome of the MS-CEBA study are the CEBA profiles, which are latent and thus need to be derived from the scores on neuropsychological tests and questionnaires used to assess the CEBA domains. Through the use of a latent profile analysis, as described in the *Statistical Analysis* section, CEBA profiles will be revealed based on the raw scores of the tests and questionnaires used.

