#### Neuropsychological tests and questionnaires assessing the CEBA domains

Table 2 lists the CEBA domains and the associated neuropsychological tests that will be used. All tests and questionnaires are commonly used in both research and clinical practice within the Netherlands, and either normative data or data from HCs  are available.

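### Deriving the profiles from raw scores over ages 18 to 70 can let age and education shape the latent classes, and the later regression on demographics cannot undo this

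*Protocol article*

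**What the plan says.** Under Primary outcome, the metric of the main result is fixed: "CEBA profiles will be revealed based on the raw scores of the tests and questionnaires used". Under Criteria, for patients and healthy controls alike, "the inclusion criteria are an age between 18 and 70 years".

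The Statistical analysis section, for 1c and 1e, sets out three steps. First, "step 1 is a latent profile analysis to identify clusters of PwMS with common CEBA profiles"; no covariate is named there. Membership probabilities follow in step 2. Then "step 3 is to relate the cluster membership probabilities from step 2 to relevant predictors", that is, "a regression analysis will be carried out to estimate the relationship between the CEBA profiles and the demographic and disease-related variables".

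The means to correct the scores are largely in hand. Table 2 records "Age, sex, education" for patients and controls, and shows the controls taking every performance test. The section on the tests and questionnaires says that "either normative data or data from HCs" are available for the instruments. Recruitment adds: "A group of 100 HCs, matched for age and education level, will be recruited through convenience sampling".

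**The concern.** Tests of speed, memory, attention and fluency commonly vary with normal ageing and education. A latent profile model that assumes independent indicators within a class has one way to account for correlation between them: it adds classes. If age moves several tests together, part of that movement can appear as a cognitive profile with no disease behind it.

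The later steps would not take it out. Step 3 relates classes already formed to demographics, so it can show an age link but cannot remove one. In 1f, profile membership could partly stand in for age. In 2a, the Phase 2 sample is recruited and assessed by the same procedure, and the test compares only the distribution of membership between samples; classes driven by age would tend to replicate in a sample of similar age mix. The planned manual then derives profiles from test scores and attaches advice to them, so a patient who is normal for their age could be placed in a cognitive profile.

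**Working it through.** The plan states no figure to reproduce. The check is whether the mechanism works at the planned size, and at what strength.

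**Inputs from the protocol article:** 300 patients; age limits 18 to 70; no covariate in step 1.

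**Assumptions:** 11 standardised indicators; ages spread evenly from 18 to 70 unless stated, so the age SD is (70 − 18)/√12 = 15.0 years; only the performance tests related to age and education; class number chosen by BIC; equal indicator variances across classes. The correlations are assumed and varied.

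**Step 1: what age and education do to the indicators.** If each performance test correlates r_age with age and r_edu with education, and these two are independent of each other, any two tests correlate at r_age² + r_edu² through demographics alone. For 0.3 and 0.3 this is 0.09 + 0.09 = 0.18.

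**Step 2: no true classes, age and education both acting** (6 performance and 5 other indicators, 25 runs per row, 1 to 4 classes fitted).

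| r_age / r_edu | Implied test-test correlation | Runs with 2 or more classes, raw | Age variance explained by class | Education variance explained | Runs with 2 or more classes, corrected |
|---|---|---|---|---|---|
| 0 / 0 | 0 | 0% | 0% | 0% | 0% |
| 0.2 / 0.2 | 0.08 | 0% | 0% | 0% | 0% |
| 0.3 / 0.3 | 0.18 | 100% | 19% | 17% | 0% |
| 0.4 / 0.3 | 0.25 | 100% | 32% | 14% | 0% |
| 0.5 / 0.3 | 0.34 | 100% | 43% | 10% | 0% |

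Corrected means residualised on age and education before fitting.

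**Step 3: no true classes, age alone acting** (7 performance and 4 other indicators, separate sets of 20 to 40 runs). At r = 0.3 (implied correlation 0.09), false classes appeared in 1/20, 4/40 and 7/40 runs. At 0.4 (0.16) and 0.5 (0.25) they appeared in every run and explained 42% to 43% and 54% to 55% of age variance. Residualising on age removed them.

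**Step 4: two true classes, 1 SD apart** (other settings as in step 2). Raw scores gave more than two classes in 0% (0.2/0.2), 12% (0.3/0.3), 76% (0.4/0.3) and 100% (0.5/0.3) of runs, with 1%, 4%, 14% and 29% of age variance explained. Corrected scores gave two classes in every run, and class explained at most 0.3% of age or education variance.

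**Step 5: a narrower age mix.** With bell-shaped ages (assumed mean 46, SD 11, cut at 18 and 70), no true classes and the same age slopes as in step 3, false classes appeared in 1/20 and 2/20 runs at the 0.4 slope, and in 17/20 and 20/20 at the 0.5 slope. This fits step 1. If the residual spread is held fixed, an age SD of 11 instead of 15 turns a correlation of 0.4 into 0.293/√(0.293² + 0.84) = 0.30, where 0.293 = 0.4 × 11/15, and one of 0.5 into 0.367/√(0.367² + 0.75) = 0.39. Cutting the tails lowers both a little further.

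**Step 6: another source of shared variation.** With a continuous factor unrelated to age (assumed loading 0.4) and still no true classes, correcting for age cut the age variance explained from 17% to 29% down to about 0.1%. BIC still chose two or more classes in 20/20 runs.

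**The case against.** The strongest reply is that the documents give neither test-age correlations nor an age distribution. The limits of 18 and 70 are eligibility bounds, and a clinic sample may cluster in middle age. The result moves from rare to universal between correlations of 0.3 and 0.4, and having no true classes at all is the worst case. This stands: a reader might infer that the profiles will be age strata, and the documents do not support that.

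Step 6 also stands. False classes are a general limit of latent profile models, so the counts in step 3 are not the price of raw scores alone. What correction demonstrably removes is the tie between class and demographics.

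It can also be said that 1e would expose an age link, that absolute ability is a reasonable predictor of participation in 1f (where the competing model uses scores rather than profiles), and that advice will also depend on the highest experienced burden, with the screening manual still to be written. These soften the consequences. They do not change how the classes are formed.

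Two further readings are tempting:

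- **The healthy-control comparison in 1b has the same fault.** It does not: controls are matched on age and education. With equal mean ages the age bias is zero. A leftover gap of 2 years, at correlations of 0.2 to 0.5, gives 0.2 × 2/15 = 0.03 to 0.5 × 2/15 = 0.07 SD. Sex is not a matching factor and no covariates are named, but covariate lists are detail that an article may leave to the analysis plan.
- **Skewed timed scores create further classes.** The article states no within-class distribution or transformation, so there is nothing on this to fault.

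**Conclusion.** The point holds as a risk that the plan creates by fixing raw scores, not as a certain outcome. As written, the primary outcome can mix normal age and education differences with MS symptoms, mainly through the performance tests, and no later step removes the mixture.

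Under the stated assumptions, distortion is absent or small at test-age correlations of about 0.2 to 0.3, unless education adds a similar effect, and substantial at 0.4 to 0.5 with a wide age spread. Real symptom classes or a narrower age mix reduce it. Analysis 1e would be partly, not wholly, a rediscovery of what shaped the classes. The change is worth making because the variables are already collected and the classes are the basis for everything that follows.

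**What to change.** In Primary outcome, replace raw scores for the performance tests with scores corrected for age, education and, where relevant, sex. Use published norms where suitable ones exist, and otherwise a regression fitted in the 100 healthy controls. The article promises norms or control data, not norms specific to age, sex and education for every instrument, so the source should be named test by test.

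An equivalent route is to enter these variables in step 1 as covariates acting on the indicators. Letting them predict class membership only would not do the same job. Either way, report the raw-score model as a sensitivity analysis, and show how far class membership tracks age and education under both.

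The cost is score preparation and one conversion step in the screening manual, with no new data. The downside is reliance on the quality of the norms, or of a regression in a convenience sample of 100. Because correction does not exclude false classes from other shared variation, the report should not present it as proof that the classes are real.

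Adding age, sex and education as covariates in 1b is optional, for precision only.
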